#### Consultation Feedback and Program Adaptation

Once the community consultations are complete, the research team will synthesize the feedback and create local adaptations of the program in conjunction with oversight and guidance provided by the Aboriginal Reference Group. Program adaptations may involve changes to illustrations, cultural elements, and language. However, the adaptations will not alter the core prevention, harm minimization, and educational components of *Strong & Deadly Futures*, which are based on a large body of existing evidence regarding effective prevention strategies in mainstream and Indigenous populations. A summary of the consultation feedback and the resulting changes will be disseminated by facilitators to the local community.

### Phase 2: School-Based Cluster RCT

#### Participants and Setting

Participants will be year 7 and 8 students from 24 government, Catholic, and independent schools in New South Wales (NSW), Queensland (QLD), and Western Australia (WA), Australia. Students in year 8 (aged approximately 12-13 years) will be the primary target group for program implementation. However, schools will also have the flexibility to enroll year 7 students owing to diversity in community needs expressed during our formative consultations [16] and variations in school and class sizes, including combined grades in smaller schools.

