#### Study Design and Randomization

This study will use a 2-group, parallel cluster RCT design. Cluster randomization by schools will be implemented, as randomizing individual students within schools would risk contamination of the control group because of student communication and peer influence effects. Recruited schools will be block randomized (ratio 1:1), stratified by geographical remoteness, to the *Strong & Deadly Futures* group (to implement the program in 2022) or the active control condition (*health education as usual* group). Allocation will be concealed and implemented by an independent statistician using the *blockrand* function in R (R Foundation for Statistical Computing) [29]. Remoteness will be classified using the Remoteness Areas structure within the Australian Statistical Geography Standard [30] and defined as metro or inner regional (major cities and inner regional) and outer regional or remote (outer regional, remote, and very remote). Randomization will occur as soon as a school is recruited and before the community consultations. To ensure that consultations are not influenced by randomization, consultation protocols will prescribe set questions for all sessions. If possible, researchers, facilitators, and participants will remain blind to allocation for the consultations; however, this will depend on consultation timing because of the requirement for schools to have sufficient time to plan class schedules. As schools and teachers play an active role in implementing the program, all schools, facilitators, and researchers will be unblinded before the trial. An overview of the study design is shown in Figure 1.

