#### Inclusion Criteria

Eligible schools will have at least 12 Aboriginal or Torres Strait Islander students per grade in 2021. Although outcomes will be measured for all students, the primary analyses will be conducted among the Aboriginal subsample in line with the focus of the study. The recruited schools are expected to vary from approximately 10% to 100% of students identifying as Aboriginal or Torres Strait Islander. All students in year 7 and 8 attending the participating schools in 2022 will be eligible to participate, provided they provide opt-in consent and their parents provide opt-in or opt-out consent (dependent upon ethical requirements; see *Informed Consent*).

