#### Assessments

Students will complete self-report surveys at pre- and postprogram implementation and at 12- and 24-month follow-up to assess program effects. Given the preventive focus of the trial, the primary end point is 24 months post baseline to coincide with the peak onset of AOD use during middle adolescence [37]. All primary and most secondary measures were administered to students in our *Strong & Deadly Futures* pilot trial. Surveys will be accessed via electronic links and captured using REDCap (Research Electronic Data Capture; Vanderbilt University) electronic data capture tools hosted at the University of Sydney [38]. REDCap is a secure research data collection platform that links participant data over time while maintaining rigorous security controls to protect students’ privacy. Students will complete surveys in class and be assured by the teacher and facilitator that the data they provide are strictly confidential. If students are absent, teachers or facilitators will arrange an alternate time to complete the survey at school. Follow-up surveys will be sent to students automatically by REDCap using the contact details supplied during the first survey. Where ethical approvals permit it, students will enter into a draw to receive an Aus $ 30 (US $ 21.67) Prezzee gift voucher (1 or 2 per school, dependent on school size) per assessment occasion to maximize participant retention. The timeline schedule for trial participants is shown in Table 1.

**Table 1 table1:** Schedule of program implementation and assessments.

	Preprogram survey	*Strong & Deadly Futures*	Postprogram survey	Booster sessions	12-month follow-up survey	24-month follow-up survey
Period	Term 3 or 4, 2022	Term 3 or 4, 2022	Term 3 or 4, 2022	Term 1 or 2, 2023	Term 3 or 4, 2023	Term 3 or 4, 2024
School grade (age group in years)	7 or 8 (11-13)	7 or 8 (11-13)	7 or 8 (11-13)	8 or 9 (12-14)	8 or 9 (12-14)	9 or 10 (13-15)
*Strong & Deadly Futures* group	✓	✓	✓	✓	✓	✓
*Health education as usual* group	✓		✓		✓	✓

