#### Demographics

Demographic variables will be recorded at baseline, including gender (*male*, *female*, *nonbinary* or *gender*
*fluid*, *different identity*, *prefer not to say*), age (12-16 years), school year (7-8), and whether students identify as Aboriginal (*Aboriginal*, *Torres Strait Islander*, *Aboriginal and Torres Strait Islander*, *not Aboriginal or Torres Strait Islander*). Socioeconomic status will be assessed using the 4-item Family Affluence Scale [39,40].

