#### Analysis

Because of the hierarchical nature of the data, outcome analyses will use multilevel mixed effects regression models (modeled using Stata [StataCorp LLC]) and take into account clustering of data at the school level. Multilevel modeling accounts for the expected correlations between repeated measurements from the same individual and between individuals in the same school, which would otherwise violate the assumptions of independence in traditional regression models. The models will take into account individual differences at baseline, estimating participant-specific starting points and change over time from these baseline levels. The randomly allocated groups (*Strong & Deadly Futures* vs *health education as usual*) will be identified by dummy-coding and entered as an independent variable. Hypothesized program effects on alcohol and tobacco uptake, psychological well-being, and secondary outcomes will be assessed by examining the allocated group-by-time interaction effects. Primary analyses will examine program effects specifically among Aboriginal and Torres Strait Islander students, with a secondary analysis conducted on the full sample. All analyses will be conducted according to the intention-to-treat principle, using all available measurements from the participants and according to their allocated group. Missing data will be accommodated based on all available information using maximum likelihood estimation.

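### Year 7 and year 8 entrants are a school year apart at the 24-month end point, and prespecifying school year and its interaction with time would recover precision for alcohol and tobacco

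*Protocol article*

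**What the plan says.** **Who enters.** Under Participants and Setting, "Students in year 8 (aged approximately 12-13 years) will be the primary target group for program implementation", yet "schools will also have the flexibility to enroll year 7 students owing to diversity in community needs". School and class sizes, and combined grades in smaller schools, are given as further reasons. Under Inclusion Criteria, "All students in year 7 and 8 attending the participating schools in 2022 will be eligible to participate". The expected share of year 7 students is not stated.

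**When they are measured.** Under Assessments, "the primary end point is 24 months post baseline to coincide with the peak onset of AOD use during middle adolescence". Table 1 pairs grade 7 or 8 at baseline with grade 9 or 10 (ages 13-15) at 24 months. No age or grade of peak onset is given.

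**How schools are allocated.** Under Study Design and Randomization, "Recruited schools will be block randomized (ratio 1:1), stratified by geographical remoteness". Also, "Randomization will occur as soon as a school is recruited and before the community consultations".

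**How the effect is tested.** Under Analysis, the allocated groups "will be identified by dummy-coding and entered as an independent variable". The effect is read from the group-by-time interaction in a multilevel model with school clustering and student-level starting points and change. No school-year term is named. The Demographics section lists school year among the baseline variables.

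**The concern.** The end point is fixed in months from baseline but justified by a stage of adolescence. Two entry grades reach it one school year apart. If use rises with age over this window, as the choice of end point presumes, entry grade should predict how much a student changes, not only where the student starts.

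The tested quantity is itself a difference in change. Student-specific starting points remove level differences between grades. Student-specific change treats a systematic grade trend as random variation and does not separate it from the arm comparison. Schools are the randomized units, so any difference in grade mix between schools has two effects:

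- it adds between-school variance in change, which lowers power;
- by chance, it can leave one arm with more year 7 students, which shifts the estimate in that realized trial.

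The argument applies to alcohol and tobacco. The article gives no comparable reason to expect a grade trend in psychological distress.

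**Working it through.** **1. The plan's own figure.** The stated minimum is 264 students in 22 schools (12 per school), for 80% power at 0.3 SD with 4 occasions. The slope-difference formula for a longitudinal cluster trial is

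n per arm = 2(1 − ρ)(z₀.₉₇₅ + z₀.₈₀)² / (K · Var(T) · slope²),

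with K = 4, T = 0 to 3, Var(T) = 1.25 and slope = 0.3/3 = 0.1. The within-student correlation ρ is not stated. With ρ = 0.58:

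2 × 0.42 × 7.849 / (4 × 1.25 × 0.01) = 131.9 per arm, which is 11 schools of 12 per arm, or 22 schools and 264 students.

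With ρ = 0.60 the result is 125.6 per arm, which also rounds up to 22 schools. For attrition, 264/0.7 = 378 (rounded up), below the 384 to be recruited. The figure can therefore be reproduced. The formula has no term for between-school variation in change and does not depend on school year.

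**2. Inputs for the grade effect.** From the article: 24 schools, 1:1, so about 12 per arm; 12 analyzed students per school; 80% power; effect 0.3 SD. Assumed: the mix of grades across schools, and a grade difference g in natural 24-month change of 0.2 to 0.4 SD. A two-sided 5% test is also assumed.

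**3. Formulas.** Let V be the between-school variance of the year 7 share.

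- Added between-school variance in change = V · g²
- Inflation = 1 + V · g² / (1/12), taking 1/12 as the variance of a school mean of 12 students
- Power = Φ(2.80/√inflation − 1.96)
- SD of the arm difference in year 7 share = √(2V/12); times g, this is the 1-SD chance shift

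**4. Results.**

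| Assumed mix | V | g | Added variance | Inflation | Power | 1-SD chance shift |
|---|---|---|---|---|---|---|
| Half year 8 only, half evenly mixed | 0.25² = 0.0625 | 0.2 | 0.0025 | 1.03 | 79% | 0.02 SD |
| Same | 0.0625 | 0.4 | 0.010 | 1.12 | 75% | 0.04 SD |
| One third year 7 only, rest year 8 only | (1/3)(2/3) = 0.222 | 0.2 | 0.0089 | 1.107 | 76% | 0.04 SD |
| Same | 0.222 | 0.4 | 0.0356 | 1.427 | 65% | 0.08 SD |

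The SD of the arm difference in year 7 share is 0.10 in the first mix and 0.19 in the second. Against the powered 0.3 SD, the chance shifts are about 7% to 14% and 13% to 26%.

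**5. Sensitivity.** With g = 0.1 SD and the second mix, inflation is 1 + 0.222 × 0.01 × 12 = 1.027 and power about 79%.

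The base variance of 1/12 is a simplification. The plan's 80% power implies a standard error of 0.3/2.80 = 0.107, and with 11 schools per arm a per-school variance of 0.107² × 11/2 ≈ 0.063. On that base the second mix gives inflation of 1.14 to 1.56 and power of about 75% to 61%. The first mix gives 1.04 to 1.16 and about 78% to 74%. An intraclass correlation, if added to the base, would lower the inflation.

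**The case against.** **The covariate list may sit in the analysis plan.** This is the strongest objection, and much of it stands. The Analysis section is a one-paragraph summary and does not say that its named terms are the only ones. School year is collected, so adjustment remains open. A reader might infer that the model excludes school year, but silence is not exclusion. What remains is that the article fixes the stratification without grade and describes its main test without grade. Naming the term is a concrete improvement on that description.

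**Year 7 entrants may not miss the intended stage.** A reader might infer that only year 8 entrants reach peak onset by 24 months. The documents do not support this. The rationale refers to middle adolescence, which is a period; no peak age is given; and Table 1 openly shows both grades at the end point. Only the one-year gap is established.

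**Grade may vary mostly within schools.** A reader might also infer that grade is a whole-school choice. The text does not say so. Adding year 7 to year 8, and combined grades in small schools, suggest mixed schools, where the grade effect partly cancels. The first mix in the table reflects this, and the loss there is small. Nor do the documents show that nearly all students start at never using.

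**Randomization protects the comparison.** If grade choice is independent of arm, there is no expected bias. Schools are allocated on recruitment and the article does not say when they settle their grades, but nothing in it shows that allocation influences the choice. Systematic bias is therefore not claimed.

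**Conclusion.** The point holds as one of precision and prespecification. Entry grade separates students by one school year at the primary end point, it is not a stratification factor, and the described group-by-time model names no term that would remove a systematic grade trend in change. With about 12 schools per arm, the cost is lost power and exposure to chance imbalance for alcohol and tobacco, without expected bias as long as grade choice is independent of arm.

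The size cannot be fixed from the documents. It rests on the assumed 0.2 to 0.4 SD grade difference and the assumed mix. Power of 79% to 75% with half the schools mixed, and 76% to 65% with none mixed, are illustrations. The lower end needs both a large grade trend and complete separation of grades by school. With a 0.1 SD trend the loss is about one percentage point even without mixed schools.

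**What to change.** In the Analysis section, or in the analysis plan before outcome data are examined by arm, prespecify baseline school year and its interaction with time as covariates in the primary models. If the analysis plan already does so, the point is met.

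Optionally, report the 24-month effect by entry grade as descriptive and supportive only. No change to the Assessments section is needed, because Table 1 already shows the grades at 24 months.

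Stratifying by grade is probably no longer available. The Results section reports all 24 schools recruited, and schools are randomized on recruitment. The adjustment needs no new data, adds no burden for schools or students, and leaves the targets of 264 and 384 students unchanged.

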#### Study Design and Randomization

This study will use a 2-group, parallel cluster RCT design. Cluster randomization by schools will be implemented, as randomizing individual students within schools would risk contamination of the control group because of student communication and peer influence effects. Recruited schools will be block randomized (ratio 1:1), stratified by geographical remoteness, to the *Strong & Deadly Futures* group (to implement the program in 2022) or the active control condition (*health education as usual* group). Allocation will be concealed and implemented by an independent statistician using the *blockrand* function in R (R Foundation for Statistical Computing) [29]. Remoteness will be classified using the Remoteness Areas structure within the Australian Statistical Geography Standard [30] and defined as metro or inner regional (major cities and inner regional) and outer regional or remote (outer regional, remote, and very remote). Randomization will occur as soon as a school is recruited and before the community consultations. To ensure that consultations are not influenced by randomization, consultation protocols will prescribe set questions for all sessions. If possible, researchers, facilitators, and participants will remain blind to allocation for the consultations; however, this will depend on consultation timing because of the requirement for schools to have sufficient time to plan class schedules. As schools and teachers play an active role in implementing the program, all schools, facilitators, and researchers will be unblinded before the trial. An overview of the study design is shown in Figure 1.

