#### Procedure

##### Recruitment

We will recruit 24 schools across NSW, WA, and QLD during 2021. Researchers will identify and approach eligible schools using data from the MySchool website [33] beginning with those who have previously expressed interest in participating. School principals and health education staff will be emailed an invitation letter detailing the study aims and procedure, followed up by phone calls or emails from the research team.

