##### Informed Consent

Once recruited, principals will be asked to provide written consent for the school to participate in the trial. Schools will distribute information and consent forms to parents electronically or by hard copy and will be required to obtain opt-in (QLD public and WA Catholic schools) or opt-out parental consent (NSW and independent schools), depending on the relevant ethical requirements. Where opt-in parental consent is required, school staff members will be reimbursed to follow a standardized script for obtaining verbal consent over the phone in cases where it is not feasible to obtain written consent from parents. Students will be provided with electronic participant information statements and consent forms before survey commencement. Only students with parental consent and who have assented will complete the survey assessments; however, all students in *Strong & Deadly Futures* schools will participate in the program, as it will be delivered as part of their usual drug education curriculum. Year 7 and year 8 health teachers will also be asked to consent to completing web-based logbooks as a measure of implementation fidelity and to permit facilitators to record their observations from the *Strong & Deadly Futures* lessons.

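### Students are consented and surveyed after their schools are randomized, and no stated safeguard keeps enrolment independent of the arm

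*Protocol article*

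**What the plan says.** All references are to the protocol article.

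- **Recruitment:** "We will recruit 24 schools across NSW, WA, and QLD during 2021".
- **Study Design and Randomization:** "Randomization will occur as soon as a school is recruited and before the community consultations". Allocation is 1:1, concealed, run by an independent statistician and stratified by remoteness only. Set questions, and blinding if possible, protect the consultations. After that, "all schools, facilitators, and researchers will be unblinded before the trial".
- **Informed Consent:** "Once recruited, principals will be asked to provide written consent for the school to participate in the trial". For parents, "Schools will distribute information and consent forms to parents electronically or by hard copy", on an opt-in basis in Queensland public and Western Australian Catholic schools and an opt-out basis in New South Wales and independent schools. Where opt-in applies and written consent is not feasible, "school staff members will be reimbursed to follow a standardized script for obtaining verbal consent over the phone". Finally, "Students will be provided with electronic participant information statements and consent forms before survey commencement". Only students with parental consent and their own assent are surveyed.
- **Participants and Setting:** year 8 is the main target, but "schools will also have the flexibility to enroll year 7 students".
- **Inclusion Criteria and Table 1:** eligible students are those attending in 2022, and baseline is Term 3 or 4, 2022.
- **Analysis:** effects are group-by-time interactions, with participant-specific starting points.

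**The concern.** Concealing the allocation protects the draw of schools. It does not protect the step at which students enter the data set, and here that step comes after the draw and is run largely by school staff. If those staff know the arm, a program school and a control school may enrol different grades, or may pursue parents with different effort where consent is opt-in.

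Grade and willingness to consent plausibly relate to how fast alcohol and tobacco use rises in early adolescence. Intention-to-treat analysis and maximum likelihood work on the students who were enrolled; they cannot restore those who never were. At stake is bias in the group-by-time effect, which is the quantity tested for all three primary outcomes.

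**Working it through.** **Step 1. Order of events.**

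| Event | Timing in the article | Relative to the draw |
|---|---|---|
| School recruited, then randomized | 2021, at once | – |
| Principal's written consent | once recruited | not ordered against the draw |
| Choice of year 7 and/or 8 | no date | not stated |
| Arm disclosed to schools, facilitators, researchers | before the trial | after; no date |
| Parental consent | no date; cohort attending in 2022 | after |
| Student assent | just before the survey | after |
| Baseline survey | Term 3 or 4, 2022 | after |

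The last three rows follow from the text. The named safeguards (concealment, set questions, blinding during consultations) cover the draw and the consultations, not enrolment. The limitations in the Discussion mention lack of blinding and attrition, but not differential enrolment.

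**Step 2. What the model removes.** Let *D* be the arm difference in the share of year 7 students, *G0* the gap in mean outcome between grades at baseline and *G24* the gap at 24 months, both in SD. Simplifying the group-by-time effect to change from baseline to 24 months:

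bias = *D* × (*G24* − *G0*)

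A gap already present at baseline and unchanged later cancels. Only different growth counts. Table 1 gives a reason why growth might differ: at 24 months one grade has reached year 9 and the other year 10, and the Assessments section places the endpoint at the peak onset of use.

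**Step 3. Illustration.** The documents give neither gap. Assume *G24* = 0.2 to 0.3 SD. With 24 schools allocated 1:1 there are 12 per arm, so if each school enrolled a single grade of similar size, *D* = 0.25 means three schools choosing differently (3/12).

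| *D* | *G24* | bias if *G0* = 0 | bias if *G0* = half of *G24* | bias if *G0* = *G24* |
|---|---|---|---|---|
| 0.25 | 0.2 | 0.05 | 0.025 | 0 |
| 0.25 | 0.3 | 0.075 | 0.0375 | 0 |
| 0.50 | 0.2 | 0.10 | 0.05 | 0 |
| 0.50 | 0.3 | 0.15 | 0.075 | 0 |

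The range 0.05 to 0.15 SD is thus the upper end, reached only if the whole gap arises after baseline.

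**Step 4. Consequence for the test.** Sample Size Calculations states 80% power at 0.3 SD and P=.05 (taken as two-sided). This implies SE = 0.3/(1.96 + 0.84) = 0.107 SD. The figure of 264 students is not in dispute and is not needed here; it can be matched only by assuming a within-person correlation, which the article does not give (0.58 to 0.60 with four equally spaced occasions). For bias *b*:

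- false-positive rate = 1 − Φ(1.96 − *b*/SE) + Φ(−1.96 − *b*/SE)
- power with bias against the program = Φ((0.3 − *b*)/SE − 1.96)

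| *b* (SD) | false-positive rate | power, bias against |
|---|---|---|
| 0 | 5.0% | 80% |
| 0.03 | 5.9% | 71% |
| 0.05 | 7.5% | 65% |
| 0.10 | 15.4% | 46% |
| 0.15 | 28.8% | 29% |

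Selective consent works in the same way, with consent status in place of grade. No figure can be put on it from the documents.

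**The case against.** The other side has several good points.

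- **Consent is partly protected.** Opt-out consent in New South Wales and independent schools leaves little room for selection. Where opt-in applies, the phone script is standardized with no distinction by arm. All students in program schools receive the program whether or not they are surveyed, so consent does not decide who is treated, and control schools receive the program later. This stands as a limit on size. A script fixes what is said, however, not how many parents are called.
- **Grade choice has reasons that predate allocation.** The article ties it to community needs, school and class sizes and combined grades, and names year 8 as the main target. A 50-point arm difference is therefore extreme. This stands, but nothing requires the choice to be fixed before the arm is known.
- **Baselines are modelled.** This stands for fixed level differences, as Step 2 shows, but not for differing trajectories.
- **Scheduling.** Schools need notice to plan classes, and baseline and program share the same two-term window. Withholding the arm everywhere until baseline is done may not be workable. This stands and shapes the fix.

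A reader might also infer that principals consent only after the draw, that grade is chosen after the draw, or that a school could decline written consent once it knows its arm. The article does not say so. Principal consent and the draw are both tied to recruitment without an order between them, grade choice is undated, and drawing an allocation is not the same as disclosing it.

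**Conclusion.** The point holds as a design risk: student enrolment and baseline follow the draw, schools and researchers learn the arm before the trial, and no stated safeguard separates the two. It is not evidence of an actual imbalance.

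The size from grade mix is the arm difference in grade share times the difference in growth between grades. The second factor is unknown. It would be tempting to read 0.10 to 0.15 SD, a third to a half of the 0.3 SD target, as the expected bias. The documents do not support that: it needs a 50-point difference in grade share and a gap that is absent at baseline and reaches 0.2 to 0.3 SD by 24 months. Smaller values, down to zero, are equally compatible with the text. The illustration concerns grade-related growth in substance use; no value is offered for psychological distress. Selective consent is a concern mainly in the opt-in schools.

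**What to change.** All 24 schools were recruited at submission, so most are probably already drawn, but data collection was still ahead. The following remains possible.

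1. For any school not yet told its arm, obtain the principal's consent and a written nomination of grade(s) and classes before disclosure. For schools already told, lock the nominated grade(s) now.
2. Fix the eligible student roll in every school at a census date.
3. Use identical, arm-neutral parental consent material and the same follow-up effort in both arms. Complete consent and baseline before disclosure where timetabling allows.
4. Include school grade and its interaction with time in the primary model. This deals with grade mix but not with selective consent, so items 2 and 3 are still needed.
5. Report consent by arm and grade against the fixed roll.
6. State in the protocol when principal consent and grade nomination occur relative to allocation and to its disclosure.

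Cost: one form per school, less flexibility on grade and, where disclosure is delayed, shorter timetabling notice. The sample size need not change.
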